#### Implementation measures

In addition to the above child and parent outcomes, we will include implementation measures [39]. Reach will be assessed by examining population participation in the intervention, including demographic representation. Adoption focuses on delivery from the primary care sites, including number of children referred through the BPA and subsequent enrollment rates. Engagement will be measured among intervention participants only, using number of total exposure hours to the intervention, including both clinic (Healthy Lifestyles) and community-based (Bull City Fit) activities. Clinic time will be recorded while the child is in clinic. A sign-in/sign-out system is used to track hours of participation at Bull City Fit. Fidelity, will be examined using the SOFIT assessment, which reports participation in the activities of the community program at a group level [57, 58], and child modifiers of participation, including social and emotional health. Maintenance will be assessed through continued engagement of primary care providers over time, and extrinsic factors that indicate likelihood of long-term sustainability, such as environmental and family influences.

### Trial study procedures

#### Data collection strategy

At the beginning of the intervention, all consented subjects (*n* = 270) have a baseline visit with a trained research assistant to collect clinical data, perform fitness testing and laboratory testing. Subjects are given an activity tracker to wear for the duration of the study. For those randomized into the intervention group, all measures for the study will be collected at routinely scheduled visits to the Healthy Lifestyles clinic at 3 months, 6 months, 9 months, and 12 months. Control subjects will have a study-only visit at baseline and at 3 months. At 6 months, control subjects will be crossed over to the intervention, and we will obtain measures at routinely scheduled Healthy Lifestyles clinic visits at 6 months, 9 months, and 12 months, which will correlate to intervention time points of baseline, 3 months, and 6 months. Clinical data are managed via REDCap, which provides a secure method of managing data to protect patient confidentiality. Surveys are completed directly in REDCap; additional are collected during study visits and as part of routine clinical care. Data are reviewed regularly for completeness. For biospecimens, participants are given a stool sample requisition kit, and either provide sample at the time of enrollment or produce sample at home. Samples are frozen immediately in a − 30 degrees (F) freezer (home or clinic), transported on dry ice, and then stored permanently at − 80 degrees (F). Serum samples for metabolomics are collected in the fasting state and immediately processed on site, and transported to the Duke Molecular Physiology Institute for further processing and storage.

#### Monitoring

We do not have a data monitoring committee, as the study is considered low risk. Because all children in the study are seen in routine clinical care, we do not have specific procedures for stopping the study or removing participants. These decisions are left to the discretion of their treating provider. As a low-risk study, we do not have planned interim analyses other than monitoring enrollment. Spontaneous adverse events are reporting in accordance with guidance from the Duke IRB.

### Biospecimen study procedures

To achieve the objectives of the biospecimen analyses, we will perform metabolomic, proteomic, and microbiomic profiling, along with stool transplants into gnotobiotic mice to test the impact of different microbiomes. For metabolomic profiling, we will use tandem flow injection mass spectrometry with addition of internal spiked standards for targeted profiling of 45 acylcarnitines and 15 amino acids [34, 59–63]. Proteomic profiling will be performed using 8 Olink targeted proteomics platforms (Cardiometabolic, Cell Regulation, CVD II, CVD III, Development, Immune Response, Inflammation, and Metabolism) giving us over 700 protein biomarkers [64–66]. For microbiome profiling, bacterial community composition in DNA isolated from stool samples will be characterized by amplification of the V4 variable region of the 16S rRNA gene by polymerase chain reaction using the forward primer 515 and reverse primer 806 following a version of the Earth Microbiome Project protocol. These primers (515F and 806R) carry unique barcodes that allow for multiplexed sequencing. Equimolar 16S rRNA PCR products from the samples will be quantified and pooled prior to sequencing. The pooled library will be submitted by the Duke Microbiome Shared Resource to the Duke Sequencing and Genomic Technologies shared resource for sequencing on a single lane of the Illumina MiSeq instrument configured for 250 base-pair paired-end sequencing runs. Microbiome bioinformatics will be performed with QIIME 22019.7 [67]. Raw sequence data will be demultiplexed and quality filtered using the q2-demux plugin followed by denoising with DADA2 (via q2-dada2) [68]. All amplicon sequence variants (ASVs) will be aligned with Mafft [69] (via q2-alignment) and used to construct a phylogeny with Raxml version 8 [70] (via q2-phylogeny). Taxonomy is assigned to ASVs using the q2-feature-classifier [71] classify-sklearn naïve Bayes taxonomy classifier against the SILVA 132 database [72].

Gnotobiotic mouse colonization will test if stool microbiome profiles from pediatric obesity patients are sufficient to phenocopy effects on host body weight and metabolic and proteomic profiles in gnotobiotic mice. Microbial communities of interest will be introduced by gavage into 12–16 week old germ-free male C57BL/6 J wild-type mice reared since weaning on a low-fat diet or moved at 6-weeks of age onto a high-fat diet. Transplanted low-fat fed and high-fat fed germ-free mice will be subsequently housed in hermetically-sealed isocages under gnotobiotic conditions [73]. Body weight will be measured at 0 and 14 days post-colonization. At baseline, 7 days, and 14 days post-colonization, plasma will be collected for metabolomic and proteomic analysis. At 14 days post colonization, animals will be euthanized and intestinal contents will be collected; liver, skeletal muscle and epididymal fat pads will be dissected, weighed, and flash frozen. Metabolomic and proteomic profiling will be performed on liver, muscle, and adipose tissue to determine the association between the candidate molecular pathways in key tissues.

Addressing potential barriers**.** We have conducted the preliminary studies to demonstrate both the feasibility of recruiting and retaining subjects using the proposed study design. However, there is the chance that we will have greater than the estimated 30% dropout. To minimize this, we will call and text families to keep them engaged. We will pair clinical and research blood sample collection where feasible. If we need to recruit more subjects, we will open additional clinical recruitment sites, including Lincoln Community Health Center, which serves many of Durham’s low-income families, or the two additional Duke Children’s Pediatric Clinics.

### Statistical analysis plan

#### Sample size

Preliminary data suggests that a meaningful difference in mean 6-month zBMI is − 0.10, and the pooled standard deviation across intervention groups is 0.2 [74]. We assume that 30% of subjects will be lost to follow-up prior to 6 months. Assuming normality of 6-month zBMI, power was computed using a two-sided t-test considering a type I error rate α = 0.05. In total, 270 subjects are needed to have 80% power to detect the meaningful difference in zBMI.

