#### Engagement in community based programs

Bull City Fit is a fitness program delivered through a local Parks and Recreation Department that provides 6 days a week of high-intensity exercise, sports and games, cooking classes, gardening, and swimming. Each session lasts 2 h and is offered to the patient and his or her family members. We have demonstrated that this program is highly engaging among a low-income, racially diverse, and ethnically diverse group. Retrospective baseline data from prior participants of the program (*n* = 500) were supplemented by key informant interviews, focus groups, and surveys to assess participant demographics, attendance, and reasons for participation. Participants believed the program helped them get healthier (96%), attend clinical appointments (85%), and feel more confident exercising in public (72%). The most common reason cited for regular attendance was that peers “look like me” (82%) [16, 17]. High levels of participation in Bull City Fit lead to measureable changes in BMI. A retrospective cohort study (*n* = 271) demonstrated a wide range of attendance, resulting in a range of 10–105 h of participation over 6 months. Higher participation was associated with greater reduction in zBMI (− 0.03 among those participating 20 h or less versus − 0.1 among those participating 80 h or more, *p* = 0.02) [16, 18]. A pilot randomized controlled trial of the clinic-community model demonstrated significantly greater contact hours, as well as improvement in physical activity and quality of life [19].

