#### Randomization

Patients who consent for participation will undergo randomization in a 1:1 ratio following the baseline visit. Randomization occurs using the Research Electronic Data Capture (REDCap) system. Research coordinators notify patients of their assigned group following the baseline visit. Given the nature of the intervention, it is not possible to blind patients or providers to treatment assignment; therefore, unblinded randomization will be conducted.

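### The printed inputs require about 184 randomised children for 80% power, not 270; either the power statement is wrong or an input that led to 270 is not printed

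*Protocol article*

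**What the plan says.** All the inputs to the primary sample size stand in the Sample size section of the protocol article, apart from the allocation ratio:

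- Target effect: "a meaningful difference in mean 6-month zBMI is − 0.10".
- Variability: "the pooled standard deviation across intervention groups is 0.2".
- Loss: "We assume that 30% of subjects will be lost to follow-up prior to 6 months".
- Test and level: "power was computed using a two-sided t-test", "considering a type I error rate α = 0.05".
- Conclusion: "In total, 270 subjects are needed to have 80% power to detect the meaningful difference in zBMI".

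The Randomization section gives the allocation: "Patients who consent for participation will undergo randomization in a 1:1 ratio following the baseline visit". The Study design section describes two arms. It also labels three groups, but Group 3 is the control children after they cross over, not a separately randomised set.

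The Sample size section mentions no design effect, multiplicity adjustment or other inflation. The General analytic approach section then analyses the 6-month change in zBMI with a generalized estimating equation model that allows for siblings being correlated.

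**The concern.** A two-sample t-test with a standardised difference of 0.5 is a standard case. It needs a little over 60 evaluable subjects per arm for 80% power, and 30% loss cannot take that to 135 per arm. The article presents 270 as the number needed, so the printed result contradicts the printed inputs. Condensing a fuller protocol does not explain this, because the section appears to give a complete set of inputs.

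What is at stake is how the trial's sensitivity is reported. If the printed inputs are right, the trial has appreciably more power for 0.10 than it claims. If an unprinted, less favourable input produced 270, that margin does not exist. A reader weighing a null result cannot tell which of these applies.

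**Working it through.** **Inputs** (Sample size section, with allocation from Randomization): difference δ = 0.10, SD = 0.2, so d = 0.10/0.2 = 0.5; two-sided α = 0.05; power 80%; loss 30%; two arms, 1:1.

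**Step 1. Try to reproduce 270.** Normal approximation, per arm:

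n = 2(z₀.₉₇₅ + z₀.₈₀)² / d² = 2(1.960 + 0.842)² / 0.25 ≈ 62.8, so 63 per arm and 126 evaluable. 126/0.7 = 180 randomised.

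The exact calculation with the noncentral t distribution gives 63.8, so 64 per arm and 128 evaluable. 128/0.7 = 182.9, so 183 randomised, or 184 with equal arms (64/0.7 = 91.4, so 92 per arm).

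The stated 270 is not reproduced: 270/184 = 1.47.

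**Step 2. Power that 270 gives.** 270 × 0.7 = 189 evaluable, or 94.5 per arm.

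Noncentrality = 0.5 × √(94.5/2) = 3.44. Normal approximation: Φ(3.44 − 1.96) ≈ 0.930. Noncentral t: 0.928. Power is therefore about 93%, not 80%.

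**Step 3. Difference detectable with 80% power at 189 evaluable.** Solving the t-test gives d = 0.410. At SD 0.2 this is 0.410 × 0.2 = 0.082.

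**Step 4. Common variants** (randomised total after 30% loss, unless noted):

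| Variant | Total |
|---|---|
| One-sided test | 146 |
| Loss applied as n × 1.3 | 168 |
| 85% power | 210 |
| 90% power | 246 |
| 95% power | 300 |
| α = 0.025 | 224 |
| α = 0.01 | 276 |
| 2:1 allocation | 205 |
| SD × √2 | 362 |
| 30% loss applied twice (128/0.49) | 261 |

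None gives 270. Two come near it, α = 0.01 and loss applied twice, but neither is what the section states.

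**Step 5. What would make 270 correct at 80% power.** Changing one item at a time:

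- SD of about 0.244 (0.10/0.410).
- Loss of about 53% (1 − 128/270 = 0.526).
- A design effect of about 1.48 (189/128 = 1.477).
- Three groups of 63 instead of two: 3 × 63 = 189, and 189/0.7 = 270 exactly.

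None of these is printed. The last is the only exact match found, and it would correspond to counting Groups 1, 2 and 3 of the Study design section separately. That origin is an inference. Because Group 3 is the control arm after crossover, the randomised two-arm comparison does not need a third set of children.

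**Step 6. Sensitivity to siblings.** If correlation between siblings acted as an inflation, a design effect of 1.2 would bring power at 270 to about 88%, and one of about 1.48 would bring it to 80%. The article gives no intraclass correlation or number of sibling pairs.

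**The case against.** The strongest defence is that the discrepancy is on the safe side. At the printed inputs the trial has more power than it claims, no estimate is biased, no analysis changes, and by April 2020, 261 of the 270 children had been enrolled (Study recruitment and enrollment). This stands, and it limits the point to a correction of a stated figure.

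A second defence is that a sibling allowance may sit in the full protocol. That is possible, but the article describes a plain t-test, and an inflation of about 1.48 would be large. The direction is not settled either. The Randomization section speaks of patients and does not mention families; where siblings fall in different arms, positive correlation reduces the variance of the contrast.

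Three stronger readings are tempting, and the document does not support them.

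- A reader might infer that the SD, or any other single input, has been shown to be wrong. Several unprinted routes lead to 270, and nothing in the text selects one.
- A reader might infer that the target effect is unknown. The section names it as 0.10; only the power for it is in doubt.
- A reader might set 0.10 against the trial team's earlier cohort in Engagement in community based programs, where zBMI changed by −0.03 "among those participating 20 h or less versus" −0.1 at 80 h or more, and conclude that the real effect is nearer 0.07 and the trial too small. That is a retrospective contrast between low and high attenders of the programme. Low attenders are not wait-list controls, so the gap does not estimate the randomised effect. The Sample size section takes its 0.10 from other preliminary data.

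On outcome wording, powering 6-month zBMI and analysing its change does not alter the expected between-group difference under randomisation. It leaves open only which SD the 0.2 is.

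**Conclusion.** The statement that 270 children are needed for 80% power is wrong as written. The printed inputs require 128 evaluable and 183 to 184 randomised. At 270 randomised with 30% lost, power is about 93% for 0.10, or 80% for about 0.082. These figures assume 1:1 allocation, equal SD of 0.2 in both arms, loss of exactly 30% in each arm, and independent children with no sibling allowance.

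The document does not show whether the power statement is mistaken or an unprinted input produced 270. At the printed inputs the error is conservative. It should be fixed because it is a stated figure that readers will rely on, but it does not threaten the primary comparison.

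**What to change.** Leave enrolment as it is and amend the Sample size section in one of two ways, according to how 270 was obtained.

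1. If the printed inputs are the intended ones, restate the power: 270 randomised with 30% loss (about 189 evaluable) gives about 93% power for a zBMI difference of 0.10 at SD 0.2, or 80% power for a difference of about 0.082, with no allowance for sibling correlation.
2. If another SD, loss rate, design effect or group count produced 270, print that input and its source so that the figure can be reproduced.

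In either case, state whether 0.2 is the SD of 6-month zBMI or of its 6-month change, since the General analytic approach section analyses change. If it is not the SD of change, redo the calculation with the SD that matches the analysis.

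The cost is two or three sentences, with no effect on recruitment, data collection or the planned model.

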#### General analytic approach

To determine the effect of the intervention on 6 month change in zBMI, a generalized estimating equation model will be fit to estimate the difference in mean change in BMI between intervention groups, using an intention-to-treat approach [75]. This model will account for repeated observations of each child as well as correlation between siblings. A similar model will be used to assess the effect of the intervention on cardiorespiratory fitness as measured by heart rate at 3 min during the step test.

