### Intervention

Subjects randomized to the intervention group enroll in the clinic-community intervention for 6 months. This includes Healthy Lifestyles clinic visits at baseline, 3-months, and 6-months, and twice-weekly sessions at the community center as described above. The clinic visits will include 30-min medical, dietary, and physical activity evaluation and counseling sessions. The sessions at the community center involve 30 min of warm up/check in time, at least 60 min of moderate-to-vigorous physical activity and 30 min of nutrition education. In total, subjects who participate fully will receive 4.5 h of clinical counseling, 52 h of physical activity, and 26 h of group-based nutrition counseling (108.5 h). In order to meet the recommended ≥26 h of contact over a 6-month period, subjects will need to participate in at least 25% of offered activities [5]. To enhance engagement and reinforce teaching, thrice-weekly text messages are sent to parent and child (if aged 11 or older, with parental permission) for the 6 months of the intervention. Within the community center, posters display playful characters designed to educate families about the experience and purpose of particular bodily sensations (e.g., Harold the Hunger Pain, Betty the Butterfly). These characters are further reinforced via text messages in which characters are reiterated, further information about that bodily sensation is provided, and information provided to increase interest in a variety of foods. Finally, monthly cartoon videos are designed to provide entertaining and accessible ways to put complex constructs like emotional eating and parent responsiveness into action.

The comparison group is an enhanced, 6-month wait list group. During the wait time, subjects will receive a non-obesity-related literacy intervention. This control intervention is consistent with Good Clinical Practice for the target population, as low-income families have fewer age-appropriate books per child in the home, and educational success is strongly mediated by literary skills [41, 42]. We will provide a $15 gift card each month to a locally owned book store in Durham. At the end of the 6-month wait time, subjects will be invited to participate in the intervention group.

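### With 30% loss assumed and 6-month BMI taken at treatment-clinic visits in both arms, the stated GEE can be biased if dropout depends on early response differently by arm

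*Protocol article*

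**What the plan says.** All references are to the protocol article.

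- **Model (General analytic approach).** "a generalized estimating equation model will be fit to estimate the difference in mean change in BMI between intervention groups, using an intention-to-treat approach". The model is to allow for repeated observations per child and for siblings. A similar model is planned for step-test heart rate. The article names no working correlation, weights, imputation or missing-data assumption.
- **Loss (Sample size).** "We assume that 30% of subjects will be lost to follow-up prior to 6 months". The paragraph on potential barriers, under Biospecimen study procedures, adds that "there is the chance that we will have greater than the estimated 30% dropout" and gives the response: "To minimize this, we will call and text families to keep them engaged".
- **6-month measurement, intervention arm (Data collection strategy).** "all measures for the study will be collected at routinely scheduled visits to the Healthy Lifestyles clinic at 3 months, 6 months", and again at 9 and 12 months.
- **6-month measurement, control arm (Data collection strategy).** Controls have study-only visits at baseline and 3 months. Then: "At 6 months, control subjects will be crossed over to the intervention, and we will obtain measures at routinely scheduled Healthy Lifestyles clinic visits". The Intervention section makes the crossover optional: "At the end of the 6-month wait time, subjects will be invited to participate in the intervention group".
- **Schedule (Table 2).** Child BMI is due at 0, 3, 6, 9 and 12 months. Fitness is due at 0, 6 and 12 months only.

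**The concern.** The primary time point is observed through a treatment clinic in both arms, but attending means something different in each. An intervention family comes if it is still engaged at the end of treatment. A control family comes if it accepts the offer to start. The study-only route used for controls at 3 months is not described at 6 months.

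The article itself gives reasons to expect attendance and response to be linked. Its Background cites poor show rates and low engagement. Its rationale sections call clinic effectiveness dose-responsive and report a zBMI change of −0.03 with 20 hours or less of community participation against −0.1 with 80 hours or more. In its pilot, families receiving texts made 4.3 clinic visits against 1.2; here thrice-weekly texts belong to the intervention.

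An unweighted GEE is not in general valid when dropout depends on earlier observed outcomes. At stake are the size of the primary effect and its 5% error rate. Fitness, the principal secondary outcome, is more exposed because it has no 3-month value for a working covariance to use.

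**Working it through.** **1. Is the 30% loss a problem of precision?** Inputs from Sample size: difference 0.10, SD 0.2, two-sided α 0.05, power 80%, loss 30%.

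- Per arm: 2 × (1.96 + 0.84)² × 0.2² / 0.10² = 62.8, so 63 (64 with the t-test).
- Total after loss: 126 / 0.7 = 180, or 128 / 0.7 = 183 with the t-test. The stated 270 is not reproduced from these two-arm inputs, which is a separate matter.
- With 270 randomised, 270 × 0.7 = 189 complete. SE = 0.2 × √(2/94.5) = 0.029, and power is about 93%.

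Precision is covered. The question is bias.

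**2. Size of the bias.** Assumptions not in the article: SD of 3-month change 0.14; correlation r between 3- and 6-month change of 0.3, 0.6 or 0.8; logistic dropout after month 3 with the log-odds shown per SD of early gain, where a positive value means poor early responders drop out more. The true effect is −0.10, with 1,000,000 children per arm, separate means by arm and visit, and 30% loss in each arm unless noted. Unweighted estimate under independence working correlation:

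| Dropout depends on 3-month change | r = 0.3 | r = 0.6 | r = 0.8 |
|---|---|---|---|
| In neither arm | −0.1004 | −0.1001 | −0.1005 |
| Both arms alike, 0.7 | −0.1002 | −0.1005 | −0.1003 |
| Intervention only, 0.7 | −0.1117 | −0.1227 | −0.1304 |
| Intervention only, 1.4 | −0.1191 | −0.1381 | −0.1502 |
| Control only, 1.4 | −0.0813 | −0.0622 | −0.0505 |
| Both arms 0.7, loss 20% control, 40% intervention | −0.1068 | −0.1145 | −0.1197 |
| Control −0.7, intervention +0.7 | −0.1229 | −0.1466 | −0.1611 |

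In the same runs, correct inverse-probability weighting gave −0.0994 to −0.1008, and a likelihood-type estimate using the 3-month change gave −0.0995 to −0.1008.

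**3. Role of the working correlation.** Actual GEE fits on 0-, 3- and 6-month zBMI, with r = 0.6, 20,000 per arm and baseline SD 0.4 (assumed):

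| Dropout | Independence | Exchangeable | Unstructured |
|---|---|---|---|
| Intervention only, 0.7 | −0.122 | −0.107 | −0.098 |
| Intervention only, 1.4 | −0.134 | −0.113 | −0.101 |

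Monte Carlo error for the independence fit is √(2 × 0.04/14,000 + 2 × 0.16 × (1/14,000 − 1/20,000)) = 0.0035, so small differences here should not be read closely. The symmetric case gave −0.108 under independence in these fits and −0.1005 in the larger run.

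A further large-sample run with no true effect, r = 0.7 and log-odds 1 in the intervention arm only gave a bias of −0.035 (independence), −0.018 (exchangeable) and 0.000 (unstructured). With the dependence in the control arm only it gave +0.036, +0.018 and 0.000.

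**4. Effect on type I error.** Take the null-case bias of 0.023 to 0.050 (independence, one arm only, r 0.6 to 0.8).

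- If change from baseline is modelled, SE = 0.029. The shifts are 0.023/0.029 = 0.79 and 0.050/0.029 = 1.72, and two-sided error is about 12% and 40%.
- If zBMI levels are modelled under independence, SE = √(2 × 0.04/94.5 + 2 × 0.16 × (1/94.5 − 1/135)) = 0.043. The shifts are 0.53 and 1.16, and the error is about 8% and 21%.

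Simulating 400 trials of 270 children with GEE fits is consistent with this. Intervention-only log-odds 1 gave a bias of −0.037 (independence) and −0.020 (exchangeable), with type I error 12–13%. Adding −0.5 in controls gave −0.056 and −0.028, with 24–28%. With dropout completely at random the error was 5.8%.

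**The case against.** Much of the case on the other side stands.

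- **The article does not say the GEE is unweighted.** A reader might infer it from silence, but weights, imputation and working correlation are commonly left to an analysis plan, and that plan is not shown. Their absence is not itself an error. An unstructured working correlation would fit the article's wording and, under missing at random, would remove the zBMI bias.
- **Bias is conditional.** A reader might infer that any dropout linked to early response biases the result. The table shows otherwise when mechanism and rate are the same in both arms. Loss that differs by arm alone (20% v 40%, unrelated to response) gave a bias of at most 0.001.
- **The direction is not fixed.** Control-only dependence biases against the intervention.
- **Leaving the sessions is not missing the visit.** Table 2 schedules the 6-month BMI without limiting it to attenders. The intervention arm is measured at the clinic after treatment ends, and families are called and texted. It goes too far to say that a child who disengages has no outcome.
- **A missing-at-random model is no complete cure.** When dropout was made to depend on the 6-month change itself, the likelihood-type estimate was still biased by −0.026.
- **Enrolment was nearly complete.** By April 2020, 261 children were enrolled, so many may have passed 6 months.

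These points narrow the concern. They leave the measurement arrangement as it is: attendance has a different meaning in each arm, and no 6-month route is described for families who do not come to the clinic.

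**Conclusion.** The concern holds in conditional form. The article's own text makes arm-specific missingness at 6 months plausible. If the GEE is fitted without weighting, dependence of dropout on the 3-month change in one arm gives a bias of about 0.02 to 0.05 zBMI under independence when r is 0.6 to 0.8. With r = 0.3 it is 0.012 to 0.019. Under exchangeable working correlation the runs gave about 0.01 to 0.03. Against the 0.10 target this is material. All these sizes rest on assumed dropout log-odds, 3-month SD and correlation, none of which the article supplies.

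Two stronger readings are not supported. The documents do not show that the primary analysis is biased, because neither the working correlation nor the dropout pattern is known. Nor does the intention-to-treat commitment fail, because analysis by assigned arm is kept. What is not assured is an unbiased estimate for all randomised children. This should be changed, but it does not invalidate the trial.

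**What to change.** 1. **Primary analysis.** Make it valid under missing at random, using the 0-, 3- and 6-month zBMI already scheduled. Options are a likelihood-based repeated-measures model with arm-by-visit terms, unstructured within-child covariance and a family effect; multiple imputation; or an inverse-probability-weighted GEE. State the missing-data assumption.
2. **Fitness.** Bring the 3-month zBMI into the imputation, weights or joint model, since no 3-month fitness value exists.
3. **Sensitivity.** Add a delta-adjusted analysis for dropout that depends on unseen 6-month weight, with the shift allowed to differ by arm.
4. **Measurement.** For children not yet at 6 months, offer height and weight under the existing study-only visit process, regardless of clinic attendance or crossover uptake, and for controls before any intervention contact.

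**Cost.** Items 1 to 3 need slightly more analysis work and no new data. Item 4 needs a short visit for non-attenders and cannot reach children already past 6 months, for whom items 1 to 3 are the only remedy.
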